#### Intervention condition

Participants in the *MatchQEP* group will receive exercise information and program sessions tailored by a QEP specifically for each BCS in the dyad. A single QEP, with advanced training on exercise for individuals with cancer, will provide all QEP sessions for each dyad. The study QEP also has research experience leading longitudinal and experimental trials while also holding a PhD in behavioral medicine. *MatchQEP* dyads will meet with the QEP via Zoom once per week for 10 weeks. Each weekly session will last up to 60 min and will include a review of the exercise program, achievement of goals/action plans set, adverse effects/events, and discussion on overcoming barriers to completing the prescribed exercise program. The actual length of the session, in minutes, will be noted. Additionally, the QEP will follow a standardized guide to deliver specific sessions each week based on behavior change counselling support strategies [54, 55] (see “Appendix”). Based on current exercise recommendations for cancer survivors [16–18], the overall goal of the QEP-prescribed exercise intervention is for each member of the dyad to complete a minimum of 150 min of MVPA per week, which may include both aerobic and resistance forms. Consistent with home-based exercise strategies, the QEP will tailor the program based on personal circumstances, including cancer-related characteristics, side effects, current fitness level, and available space and equipment [16]. *MatchQEP* group participants will have the opportunity to reach out to the QEP individually if they need to ask specific and personal questions during the intervention period. For 4 weeks following the completion of the 10-week intervention, the QEP will be available for consultation (i.e., a post-intervention tapering period) as needed by the *MatchQEP* group participants. This tapering period is important for understanding strategies to successfully taper BCS from exercise trials. All interactions between the QEP and the dyads from intervention initiation until the end of the tapering period will be recorded.

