#### Control condition

BCS in the *Match* (control) group will independently communicate and support each other around exercise for 10 weeks. They will not have any contact with a QEP during this time and will structure their own communication with their matched peer. After the 12 weeks post-intervention follow-up assessment (26 weeks post-baseline), BCS in this group will be offered a single consultation session with a QEP to discuss exercise-related questions.

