#### Cost-effectiveness

The costs of the *MatchQEP* intervention will be calculated and compared to traditional face-to-face costs of QEP services in Canada and to the *Match* group alone. Refer to Table 2 for a description of costs to be compared between *MatchQEP* group and traditional QEP services. The use of health care resources will also be compared between the two groups at the post-intervention, post-tapering, and follow-up time points using a piloted questionnaire [68] that assesses health care facility visits, doctor visits, procedures received, support services used, and loss of work (see Additional file 2).

**Table 2 Tab2:** Cost of *MatchQEP* group versus traditional QEP services

*MatchQEP group*		
Program costs^#^	Professional time/labor	# of contact hours × unit cost of Qualified Exercise Professional (QEP) over the 10-week intervention period and 4-week tapering period*
	Equipment	Any device a survivor may purchase (pay out of pocket) for use at home based on the QEP’s recommendation (such as TheraBand or free weights) Computer for QEP
*Traditional QEP services*		
Session costs^#^	Total cost of QEP session	Includes venue use/cost of membership, equipment at venue, preparation time for the QEP
	Labor	# of QEP sessions attended during a comparable 10-week period × cost of each session
Travel	Mileage estimates	Based on distance (km) from an individual’s home to the session venue and the cost of gas (/km)
	Public transportation costs	
	Parking costs	
Home-based equipment		Any form of device that a survivor may purchase for use at home based on the QEP’s recommendations (for example, TheraBand or free weights)
Consumable materials	Photocopies of home exercises	
	Printed letters/folders given to survivors	

^*^For each 1-h contact cost, 1.5 h of labor will be allocated to account for the preparation time required for each session

^#^The cost of training staff will be excluded as staff will already be qualified for their role

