#### Safety/adverse events

While exercise is known to be safe for BCS when performed correctly [14, 15], minor injuries have the potential to occur in any exercise intervention. To enhance participant safety in this study, all participants will be cleared to exercise prior to enrollment using the PAR-Q+/ePARmed-X+, [72] with physician clearance as needed. For the women in the *MatchQEP* group, tailored exercise recommendations will be provided during the exercise program delivery. Any injuries or side effects that occur in the *MatchQEP* group will be tracked by the QEP on an ‘events’ log with all adverse events classified on severity with specific types/class using the “Common Terminology Criteria for Adverse Events”. Adverse events will be reported to the Principal Investigator immediately for follow-up with BCS and connection to physician for further consultation.

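### Active adverse-event tracking is specified for MatchQEP only, so harms cannot be compared between arms and injuries in Match have no stated path to follow-up

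*Protocol article*

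**What the plan says.** The Safety/adverse events section accepts that "minor injuries have the potential to occur in any exercise intervention". Two provisions follow. The first covers everyone: "all participants will be cleared to exercise prior to enrollment". The second covers one arm: "Any injuries or side effects that occur in the *MatchQEP* group will be tracked by the QEP", on an events log, with severity and type classified by CTCAE. Reported events go to the Principal Investigator for "follow-up with BCS and connection to physician for further consultation".

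The Intervention condition section adds active enquiry in MatchQEP. Each of the 10 weekly sessions "will include a review of the exercise program, achievement of goals/action plans set, adverse effects/events". The Control condition section says of Match women: "They will not have any contact with a QEP during this time". Their first offered QEP session comes only after the week-26 assessment.

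One other source covers both arms. The Cost-effectiveness section says "The use of health care resources will also be compared between the two groups at the post-intervention, post-tapering, and follow-up time points", by a questionnaire that "assesses health care facility visits, doctor visits, procedures received, support services used, and loss of work".

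**The concern.** Both arms take part in an exercise intervention. Under the Intervention section every woman receives a peer support guide, an infographic on exercise guidelines and a Fitbit, and Match dyads support each other around exercise for 10 weeks. Injuries can therefore arise in either arm. The only recorder the article names is the QEP, whom Match women do not meet during that period.

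Two things are at stake. First, the trial asks what adding QEP support does, and harm is a natural part of that question. When one arm is asked every week and the other is not described as being asked at all, a difference in recorded events cannot be separated from the difference in asking. Second, the follow-up step depends on an event reaching the study team, and no such path is described for Match.

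**Working it through.** The article states no adverse-event rate and no harms calculation, so there is no figure to reproduce. The check is to set the provisions for the two arms side by side.

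| Provision | MatchQEP | Match | Section |
|---|---|---|---|
| Clearance before enrollment | Yes | Yes | Safety/adverse events |
| Enquiry at weekly sessions, weeks 1 to 10 | Yes | None described | Intervention condition; Control condition |
| Events log with CTCAE grading | Yes, kept by the QEP | None described | Safety/adverse events |
| QEP available as needed, weeks 10 to 14 | Yes | No | Intervention condition; Control condition |
| Health care use questionnaire, weeks 10, 14 and 26 | Yes | Yes | Cost-effectiveness; Data collection and measures |

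1. Clearance is screening. It takes place before exposure and records no events.
2. The log and the weekly enquiry both run through the QEP, so both are confined to MatchQEP.
3. The health care use questionnaire is symmetric, but it is described as counting visits, procedures, services and lost work for costing. No injury item, severity grade or link to exercise is described. It would miss an injury that led to no care and no lost work, which is likely for the minor injuries the safety section has in mind.
4. The other questionnaires listed under Data collection and measures cover exercise, social support, quality of life and sedentary behavior. None is described as asking about injuries.

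The size can be illustrated only under assumed risks. The Sample size section gives 54 dyads, and allocation is 1:1, so each arm has 54 / 2 = 27 dyads, or 27 × 2 = 54 women. The expected number of Match women with an event is 54 × risk:

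- 5%: 54 × 0.05 = 2.7
- 10%: 54 × 0.10 = 5.4
- 20%: 54 × 0.20 = 10.8
- 30%: 54 × 0.30 = 16.2

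Unequal capture can also distort a comparison. Suppose the true risks were 10% in MatchQEP and 20% in Match, with full capture in MatchQEP. If half the Match events were captured, the recorded risks would be 10% and 0.20 × 0.5 = 10%. If none were captured, they would be 10% and 0%. A real benefit would be hidden in the first case and reversed in the second. The risks and capture shares are assumptions chosen to show direction. None comes from the article.

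**The case against.** The strongest reply is that the article plans no comparison of harms. Safety is not a primary, secondary or tertiary outcome, Table 1 has no safety hypothesis, and the Statistical analysis section has no test of adverse events. This stands. A reader might infer that the trial, run as written, will report a spurious significant excess of harm in MatchQEP. The documents do not support that: no such test is proposed, and any probability put on it would rest on assumed event rates and on zero capture in Match.

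It can also be said that zero capture is read from silence. The sentence on reporting to the Principal Investigator names no arm, women in both arms deal with study staff, and the items of the health care use questionnaire are in an additional file that is not at hand. This stands in part. Spontaneous reports from Match are possible, and medically attended events may leave a trace. But the article does more than leave a detail to a fuller document. It states a rule for one arm and ties it to a person the other arm does not meet.

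A reader might further infer that physician referrals following logged events bias the doctor-visit comparison against MatchQEP and should be removed. The documents do not establish this. The size is unknown, tailored guidance could also lower visits, and contacts prompted by the QEP are arguably a real consequence of adding QEP support that a cost comparison should count.

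**Conclusion.** The asymmetry is established from the text: active event tracking is specified for MatchQEP, and none is described for Match. Two consequences follow. Any between-arm statement about harms would be uninterpretable, and a Match injury has no stated path to the follow-up step. It does not follow that every safety statement is invalid, because an account of events within MatchQEP would stand. The primary outcome, the dyadic models and the other planned efficacy analyses are unaffected.

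The size is unknown because no event rate is given. The illustrative 2.7 to 16.2 Match women assume risks of 5% to 30% and full recruitment of 54 women per arm. The conclusion assumes that documents not shown do not already provide matching event capture in Match. This is a worthwhile improvement to safety reporting and participant follow-up. It is not a flaw that threatens the trial's main result.

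**What to change.** - Add the same short injury and adverse-event items to the online questionnaires that both arms already complete at weeks 10, 14 and 26.
- State in the safety section that the route for reporting an event to the study team applies to both arms.
- Base any between-arm statement about harms only on these common items.
- Report the QEP log separately, as a description of MatchQEP.

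The cost is a few questionnaire items and a few sentences. The downside is that events recalled over several weeks are less detailed than a weekly log and minor ones may be forgotten, but the loss is then of the same kind in both arms. The items should be in place before the week-10 assessments, because events not asked about then are hard to recover later. If they cannot be added, the protocol should at least say that harms will be described for MatchQEP only and not compared. That would settle the interpretation but leave the follow-up gap in Match.

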### Statistical analysis

All analyses will be conducted using R [73] and MPlus 7.4 [74]. Significance will be established at *p* < 0.05 for all coefficients. Descriptive statistics (means, frequencies, zero-order correlations) will be computed for all measures over time. The main analysis will be guided by APIM [41] to explore interpersonal and individual effects of the intervention (QEP support) for the primary and secondary outcomes over time.

In the APIM (see Fig. 1), effects of both dyad members are assessed simultaneously by estimating interpersonal peer effects (labelled partner effects in APIM) and individual effects (labelled actor effects in APIM). Three types of effects can be used to explore the research questions examining MVPA among BCS. First, the peer (i.e., partner) effects indicate the average influence of each BCS’s MVPA in the dyad. Second, the actor effects assess the average stability of MVPA across the intervention for each dyad member. Specifically, actor effects provide an indication to the effectiveness of the QEP support intervention since MVPA is assumed to be altered by QEP support more strongly when compared to the control group. Third, the average intervention effects will be tested and compared to post-intervention MVPA. The effectiveness of matching BCS dyads on device-measured MVPA, social support, and HRQOL will also be explored in separate models testing actor and partner effects on these secondary outcomes.

Multiple-group structural equation modeling (SEM) will be used to estimate and test an APIM with two groups (*MatchQEP* vs. *Match*). To address research question 1, the mean post-intervention levels of MVPA (controlling for actor and partner effects) of the two groups will be compared. For research question 2, the average partner (i.e., peer) effects of MVPA from each BCS in the dyad will be estimated within each group [43]. The effects will be tested by comparing constrained and unconstrained models on chi-square goodness-of-fit values. For research question 3, the average actor effects for MVPA among BCS will be estimated for the *MatchQEP* and *Match* groups and will be tested against each other. These analyses will be repeated for device-measured MVPA, social support, and quality of life (secondary outcomes). Measured covariates (e.g., cancer and personal characteristics, partner characteristics and quality of match, therapeutic alliance) will be included in the models as necessary based on their association with the outcomes.

To assess the intervention effects (tertiary outcomes)*,* adherence will be examined based on the number of sessions attended with the QEP in the *MatchQEP* group and on the frequency the peers connected over the duration of the study for both *MatchQEP* and *Match* participants. Cost-effectiveness will be determined by comparing the direct intervention costs between study groups and between the *MatchQEP* group and traditional, in-person QEP services. Additionally, cost-effectiveness of the intervention group, compared to control group, will be calculated based on the intervention costs per participant with respect to changes in the assessed health outcomes. Incremental cost-effectiveness ratios will determine the cost of one unit of change for the investigated outcomes. Mean costs of each category of health resource use (health care facility visits, doctor visits, procedures received, support services used) and loss of work will be calculated for each group and compared for significant differences using *t* tests. All costs will be determined based on current 2021 Ontario Health Care standards in Canadian dollars.

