### Data collection and measures

Following informed consent, all BCS will complete a demographics questionnaire, including questions related to peer matching criteria, treatment, and exercise history. To determine the effectiveness of the intervention, BCS will complete exercise volume, social support, and HRQOL questionnaires online at four time points: baseline, post 10-week intervention, post 4-week tapering (i.e., 14 weeks post-baseline), and at 12 weeks post-intervention follow-up (i.e., 26 weeks post-baseline). BCS will be asked to wear the Fitbit to collect device-measured MVPA for one week at all four timepoints. Self-reported sedentary behavior will be assessed as a potential covariate at all time points. The QEP alliance (i.e., connection to the QEP support provider) will be assessed as a covariate at post-intervention and post-tapering time points. Adherence to the intervention will be calculated at the end of the intervention period (10 weeks) and cost-effectiveness will be assessed at post-intervention (10 weeks), post-tapering (14 weeks), and at the 12-week post-intervention follow-up (26 weeks after baseline assessment).

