### Descriptive data and covariates

Age in years, stage of cancer, time since treatment, time since diagnosis, current medications, and exercise preferences will be self-reported at baseline in an online demographic questionnaire. The Sedentary Behavior Questionnaire [69] will be used to assess the amount of time (in hours) per week spent engaged in sedentary pursuits (e.g., watching television, sitting and reading). The scale has demonstrated reliability and validity in adult populations [69]. Sedentary behavior will be a covariate [70]. Exercise peer match quality (assessed on a 5-point scale from 1: very poor match to 5: very good match), amount of time spent with peer, method of connecting with peer, and perceived similarities with peer (assessed on a 5-point scale from not at all similar to extremely similar) will be collected post-intervention and used as covariates in analyses (see Additional file 3). Therapeutic alliance between participants and the QEP will be assessed by each participant in the *MatchQEP* group at the post intervention (10 week) and post tapering (14 week) time points using the modified Work Alliance Inventory—Short Form Revised (WAI-SR) [71]. The WAI-SR is a twelve-item scale evaluating three domains of therapeutic alliance: (1) agreement between patient and therapist on the goals of treatment, (2) agreement between patient and therapist about the tasks to achieve these goals, and (3) the quality of the bond between the patient and therapist (QEP) [71]. Each item is assessed on a 7-point Likert scale from 0 (never) to 7 (always), with higher scores representing higher satisfaction with the therapist (QEP)-patient relationship [65]. The WAI-SR is a reliable and valid outcome for assessing therapeutic alliance (internal consistency: α = 0.91, test–retest reliability: *r* = 0.93; and construct validity: *r* = 0.74) [71].

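### The covariate rule lets the treatment comparison adjust for variables measured after the intervention, and for alliance, which exists only in MatchQEP; the randomised effect may be distorted

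*Protocol article*

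**What the plan says.** The Statistical analysis section describes a multiple-group structural equation model. Research question 1 compares the two groups on mean post-intervention MVPA, controlling for actor and partner effects, and the analyses are repeated for the secondary outcomes. It then adds: "Measured covariates (e.g., cancer and personal characteristics, partner characteristics and quality of match, therapeutic alliance) will be included in the models as necessary". The same sentence gives the rule for choosing: covariates "will be included in the models as necessary based on their association with the outcomes".

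Descriptive data and covariates gives the timing. Match quality, time with the peer, method of connecting and perceived similarity "will be collected post-intervention and used as covariates in analyses". The same section says who has an alliance score: "Therapeutic alliance between participants and the QEP will be assessed by each participant in the *MatchQEP* group". Data collection and measures gives alliance its role: "The QEP alliance (i.e., connection to the QEP support provider) will be assessed as a covariate at post-intervention and post-tapering time points". Under Control condition, the Match women have no QEP to rate: "They will not have any contact with a QEP during this time".

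On sedentary time, Data collection and measures says: "Self-reported sedentary behavior will be assessed as a potential covariate at all time points". Descriptive data and covariates lists it as a covariate without saying which time point's value is used.

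**The concern.** Randomisation protects the comparison of MatchQEP with Match only while the analysis conditions on things that allocation cannot have changed. Four of the named covariates are recorded at the same time as the primary endpoint and describe the peer relationship. The protocol expects QEP support to work on that relationship. Study purpose says the QEP should help dyads support each other's MVPA, and week 4 of the Appendix programme covers connection, communication and support strategies.

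If QEP support improves the match or increases contact, and these in turn raise MVPA, adjusting for them subtracts part of the effect that research question 1 asks about. If they merely share an unmeasured cause with MVPA, such as motivation, adjustment opens a spurious path between group and outcome. The problem is sharper for social support as an outcome, because perceived match quality and peer contact lie close to the outcome itself.

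Alliance raises a different problem. It has no value in the control group, so it cannot adjust a between-group difference in the ordinary sense.

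**Working it through.** **No stated figure to reproduce on this point.** The protocol gives no expected treatment difference. Its only design calculation is the number of dyads needed for the actor and partner effects (32 and 43). An indistinguishable-dyad formula with the stated inputs (0.33, 0.28, baseline correlation 0.46, error correlation 0.30, two-sided alpha 0.05 assumed, power 0.80) gives 31 and 42. That calculation contains no covariates and is unaffected.

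**Step 1. The covariates side by side.**

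| Covariate | When measured | In whom | Could QEP support shift it? |
|---|---|---|---|
| Age, stage, time since treatment | Baseline questionnaire | Both groups | No |
| Match quality, time with peer, method of connecting, similarity | Post-intervention | Both groups | Plausibly (Study purpose; Appendix, week 4) |
| Sedentary time | All four time points | Both groups | Later values, plausibly |
| Therapeutic alliance | Weeks 10 and 14 | MatchQEP only | Exists only because of QEP support |

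**Step 2. Adjusting for a post-intervention peer variable.** All values here are assumptions. Let the true effect be 0.50, with the outcome in units of roughly one SD. Let g be the shift that treatment produces in the covariate (in its within-group SDs), d the covariate's own effect on the outcome, and u the path from an unmeasured common cause to each of covariate and outcome. Within group, the slope of outcome on covariate is d + u², so

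adjusted effect = 0.50 − g × (d + u²).

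| g | Mediator only (d = 0.3, u = 0) | Shared cause only (d = 0, u = 0.4) | Both |
|---|---|---|---|
| 0 | 0.50 | 0.50 | 0.50 |
| 0.3 | 0.50 − 0.3 × 0.30 = 0.41 | 0.50 − 0.3 × 0.16 = 0.45 | 0.50 − 0.3 × 0.46 = 0.36 |
| 0.5 | 0.35 | 0.42 | 0.27 |
| 0.8 | 0.26 | 0.37 | 0.13 |

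Least-squares simulation of a dyad-randomised trial agrees with every cell to within about 0.01. Without the covariate it returns about 0.50 throughout. If the common cause acts in opposite directions on covariate and outcome, the bias is upward: with g = 0.3 and a path product of −0.16, the result is 0.50 + 0.3 × 0.16 = 0.55.

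**Step 3. The selection rule.** The factor d + u² is the within-group association between covariate and outcome, which is what the rule screens on. A post-intervention variable with no such association leaves the effect at 0.50 and would be left out. Those that move the effect are the ones likely to be kept.

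**Step 4. Alliance in the MatchQEP equation only.** Let alliance have mean m and slope b in MatchQEP, and enter as its deviation from a reference value c. The contrast of group intercepts is

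0.50 − b × (m − c).

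With m = 5 (assumed) and c = 0, the bottom of the 0 to 7 scale:

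- b = 0: 0.50
- b = 0.1: 0.50 − 0.1 × 5 = 0.00
- b = 0.2: 0.50 − 0.2 × 5 = −0.50

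Simulation of the last case with 108 women, alliance SD 1 and controls coded 0 gives a mean of −0.52 and a standard error of 0.73. That coding is algebraically the same as one-group inclusion without centring. Centring alliance at its MatchQEP mean gives 0.50 with a standard error of 0.19. The simulation ignored correlation within dyads, so the standard errors serve only for comparison with each other.

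**The case against.** The strongest reply is that the text is conditional. The covariate list is given as examples, inclusion is only as needed, and the sentence on research question 1 names only actor and partner effects as controlled. This is fair as far as it goes, and it rules out saying that the primary model will certainly contain these variables. But the condition is association with the outcome, not timing. The covariate sentence follows the description of all three research questions without exempting any. The statement that the peer variables are used as covariates carries no condition.

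A reader might infer that including alliance deletes every control dyad and makes the treatment effect inestimable. The documents do not support that. They nowhere specify complete-case handling, and a multiple-group model can carry alliance in one group and still be fitted. What stands is the reference-value problem in step 4. Centring removes it, but the protocol does not mention centring.

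A reader might also infer that sedentary time is adjusted for at the same visit as the outcome. The text does not say whether the baseline or a later value is used, so this is a gap to close and not a stated error.

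Finally, match quality and similarity partly reflect the matching done before allocation, and nothing shows that QEP support shifts them. That is correct: with g = 0 there is no bias. The protocol's own rationale nevertheless predicts a shift.

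**Conclusion.** The point holds as a risk created by a stated rule. The protocol allows the randomised comparison, for the primary and secondary outcomes, to be adjusted for post-intervention peer variables and for a variable that exists in one group only, chosen by observed association with the outcome. The adjusted contrast may then no longer estimate the effect of adding QEP support.

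It would go too far to say that the comparison is biased. Size and direction cannot be known from the documents, and bias requires that treatment shift the covariate. The range of 0.13 to 0.45 for a true 0.50 rests on assumed shifts of 0.3 to 0.8 SD and assumed paths of 0.3 and 0.4, and opposite-signed paths would push the estimate upward. The alliance figures likewise rest on an assumed mean and slope. The baseline cancer and personal characteristics in the same list are unobjectionable. No separate harm has been shown for the within-group actor and partner effects of research questions 2 and 3.

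**What to change.** In the treatment-comparison models for all outcomes:

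- Adjust only for covariates measured at screening or baseline, before the intervention starts, and named in advance: the baseline outcome of actor and partner, plus a short list such as the matching discrepancy scores already planned under Intervention.
- Do not word this as pre-randomisation covariates only. Treatment allocation and randomization places allocation before the baseline assessment, so that wording would exclude the baseline MVPA scores on which the actor-partner model depends.
- If sedentary behaviour is used, state that only its baseline value enters.
- Delete selection by association with the outcome.

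Move match quality, time with the peer, method of connecting, perceived similarity and post-baseline sedentary time to analyses labelled exploratory or mediation. Analyse alliance within MatchQEP only.

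The cost is wording in the analysis section. Data collection, visits and sample size do not change, and every variable is still used.
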